#### *Randomised controlled trial*

Children aged 5 months with a moderate to severe skull deformation, measured by PCM are eligible for the RCT. PCM is a reliable, valid, non-invasive and easy-to-use method for measuring the shape of the skull [35,36]. To determine the severity of deformational plagiocephaly, the oblique diameter difference index (ODDI) is used. This is the ratio between the longest and the shortest oblique diameter, multiplied by 100%. Both diameters are located at 40° from the anterior-posterior line. A moderate to severe plagiocephaly is defined as 108% ≤ ODDI ≤ 113%. The severity of deformational brachycephaly is established with the cranio proportional index (CPI). This is the ratio between the width and the length of the skull and is considered to be moderate to severe when 95% ≤ CPI ≤ 104%. Mixed forms with ODDI > 106% and CPI > 92% are also included. Exclusion criteria are similar to those at T0.

At T5, children meeting RCT eligibility criteria can still enrol in the study (late-enrolment).

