### Sample size

The required sample size for the HEADS RCT, based on a significance level of 5%, power of 90% and a difference in mean improvement of at least 4 ODDI-points (SD 6 ODDI-points) was calculated as 72 infants (36 in each arm). Assuming a maximum estimated loss-to-follow up of 25%, we needed to include 96 children in the RCT.

In 2008, a preliminary study was performed into the feasibility of an RCT on helmet therapy for skull deformation. Of the parents of 61 children with a skull deformation, 39% agreed to participate in a study as described in the patient information and verbally clarified. In the light of this information, the size of the current study region was chosen and the inclusion period was estimated.

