#### *Randomised controlled trial*

At T5, characteristics of the RCT population will be described. In a subsequent analysis, the intervention and control group will be compared with respect to prognostic factors using the independent samples *t*-test or the chi square test. The representativeness of the RCT population will be determined by comparing baseline demographic and clinical characteristics of the RCT population with those of the total eligible population at T5. Both the change score (continuous variable) and the success of recovery (dichotomous variable) will be compared between groups on an intention-to-treat basis. After analysis of covariance (ANCOVA), both multiple regression analyses (change score) and logistic regression analyses (success of recovery) will be carried out with predictor variables to control for confounders. Finally, a per-protocol analysis will be performed.

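### The RCT is sized on ODDI alone although infants can enter on CPI alone, so an all-infant ODDI comparison probably estimates less than 4 points, and 36 per arm gives about 80% power, not 90%, even before that dilution

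*Protocol article*

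**What the plan says.** **Sizing.** The Sample size section of the protocol article uses one index only: "a difference in mean improvement of at least 4 ODDI-points (SD 6 ODDI-points", "based on a significance level of 5%, power of 90" per cent. The result "was calculated as 72 infants (36 in each arm") is then inflated: "Assuming a maximum estimated loss-to-follow up of 25%, we needed to include 96 children in the RCT". No allowance is made for type of deformity.

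**Entry.** Eligibility criteria, Randomised controlled trial, gives three routes.
- Plagiocephaly: "A moderate to severe plagiocephaly is defined as 108% ≤ ODDI ≤ 113" per cent.
- Brachycephaly, which "is considered to be moderate to severe when 95% ≤ CPI ≤ 104" per cent, with no ODDI minimum.
- Mixed forms: ODDI above 106% together with CPI above 92%.

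The same section defines ODDI: "This is the ratio between the longest and the shortest oblique diameter, multiplied by 100" per cent.

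**Outcome and analysis.** Under Primary outcome, skull shape at 24 months is described by ODDI for plagiocephaly, CPI for brachycephaly, and ear deviation. There is a continuous change score and a full-recovery outcome (ODDI below 104% and CPI below 90%). Statistical analyses, Randomised controlled trial, states: "Both the change score (continuous variable) and the success of recovery (dichotomous variable) will be compared between groups on an intention-to-treat basis". It names no index for the change score and sets no restriction by type of deformity.

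**The concern.** An index that measures asymmetry has little room to improve in an infant admitted for symmetric flattening. If ODDI change is compared over everyone randomised, the mean difference averages infants who can respond on that index with infants who have little to gain on it. The same holds in reverse for CPI. An infant who enters on ODDI alone has CPI of at most 92%, close to the recovery cut-off of 90%.

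Two things are at stake. The first is the meaning of the estimate: an all-infant ODDI difference below 4 points could reflect case mix as much as treatment. The second is the power claim, which rests on a 4-point difference and which the stated group size does not support even when that difference is granted in full.

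**Working it through.** **1. The plan's own figure.** Inputs from Sample size: difference 4, SD 6, alpha 0.05 (sidedness not stated, two-sided assumed), power 0.90. The normal-approximation formula is n per arm = 2[(z₁₋α/₂ + z_power) × SD / difference]².

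- 90% power: 2 × [(1.960 + 1.282) × 6/4]² = 47.3, so 48 per arm, 96 in all. The stated 72 is not reproduced.
- 80% power: 2 × [(1.960 + 0.842) × 6/4]² = 35.3, so 36 per arm, 72 in all. This matches exactly.
- One-sided 5%, 90% power: 39 per arm, 78 in all. No match.
- With the t-distribution, two-sided: 48.3 per arm for 90% and 36.3 for 80%. Power at 36 per arm is 79.7% (80.7% by the normal approximation).
- The loss step is correct: 72/(1 − 0.25) = 96. From 96 evaluable infants it would be 96/0.75 = 128.

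**2. Room to improve in brachycephaly-only infants.** An infant entering on CPI of 95% or more already exceeds the 92% CPI limit for mixed forms. With ODDI above 106% it would therefore count as mixed, so a brachycephaly-only infant has ODDI of at most 106%. ODDI is longest over shortest diameter, so its floor is 100%, and the room is at most 106 − 100 = 6 points. Unless controls worsen, a 4-point difference between arms needs a baseline of 104–106%, near-complete correction with a helmet, and at most 6 − 4 = 2 points of natural recovery in controls. An infant already below 104% has less than 4 points to lose.

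**3. Dilution.** Let p be the brachycephaly-only share, d_b the ODDI difference between arms in that subgroup and s_b its SD. None of these is in the document; all are assumptions. Infants with plagiocephaly or mixed form keep difference 4 and SD 6.

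- All-infant difference = 4(1 − p) + d_b p
- All-infant SD = √[36(1 − p) + s_b² p]
- The restricted analysis keeps difference 4 and SD 6, with 36(1 − p) per arm.

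Example: p = 0.25, d_b = 0, s_b = 6 gives a difference of 4 × 0.75 = 3.0 and SD 6. With s_b = 2 the SD is √(27 + 1) = 5.29.

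Power, two-sided t-test, 36 per arm overall:

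| p | Difference (d_b = 0) | All infants, d_b = 0, s_b = 6 | All infants, d_b = 0, s_b = 2 | All infants, d_b = 1, s_b = 2 | Restricted to ODDI > 106% |
|---|---|---|---|---|---|
| 0.10 | 3.6 | 71% | 75% | 77% | 75% |
| 0.25 | 3.0 | 55% | 66% | 73% | 67% |
| 0.40 | 2.4 | 39% | 55% | 68% | 57% |

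With d_b = 1 the all-infant differences are 3.7, 3.25 and 2.8. With d_b = 2 and s_b = 2, all-infant power stays at about 79% for all three shares, while the difference is still only 3.8, 3.5 and 3.2. The SD formula pools within deformity types and ignores differences in mean change between types, which would lower the all-infant power somewhat.

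**The case against.** **The document does not commit to ODDI change in all infants.** A reader might infer this from the Sample size section, but it is not written. Primary outcome links ODDI to plagiocephaly and CPI to brachycephaly, so an analysis by type of deformity would fit that text. A condensed article may also leave the index to a fuller plan. This stands. The sizing assumption, however, is stated, and it makes no allowance for infants admitted on CPI alone.

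**A 4-point difference is not impossible in brachycephaly-only infants.** A reader might conclude that they cannot contribute it. With up to 6 points of room, that goes too far; very unlikely is the right strength. The 4 points are also a mean, not a figure for every infant. The population behind the 4 and the SD of 6 is not described, so these values may already reflect mixed entry. That is why the dilution is called probable and not certain.

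**Restriction does not always gain power.** It does so at every share in the table only when the subgroup has no effect, and the clear gain needs SD 6 as well. That SD sits badly with infants who have so little room to change. With SD 2 and no effect the two analyses are nearly equal. With SD 2 and a 1-point effect the all-infant analysis has more power at every share.

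**An effective treatment would not necessarily be missed.** Full recovery uses both indices, covers every infant and is already compared by intention to treat.

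**The shortfall from 90% is not all dilution.** At a 10% share with SD 6 and no subgroup effect, about 10 of the 19 missing points (90 to 80) come from the sample-size arithmetic and about 9 (80 to 71) from dilution. ANCOVA could bring 36 per arm to 90% if baseline and outcome correlate at about 0.49, but no such correlation is stated. One-sided testing does not rescue the figure: 36 per arm would then give 88%.

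**Conclusion.** The point holds in a limited form. Two parts are firm. On the stated inputs, two-sided, 36 per arm gives about 80% power, and 90% needs about 48 per arm. The entry criteria also cap ODDI at 106% in infants admitted on CPI alone, which leaves them at most 6 points to lose.

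The rest is probable and depends on assumptions. If ODDI change is compared over all infants, the expected difference falls below 4 whenever the brachycephaly-only difference is below 4 and the planned 4 points describe infants with ODDI deformity. With no ODDI effect in that subgroup it is 3.6, 3.0 or 2.4 points at shares of 10%, 25% or 40%. The corresponding power is about 71–75%, 55–66% or 39–55% for a subgroup SD between 6 and 2. The true share, subgroup SD and subgroup effect are not in the document, so the size of the loss cannot be fixed. The documents do not support saying that the trial is bound to an all-infant ODDI analysis, or that restricting it must raise power.

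**What to change.** 1. Correct the power statement. Give the power for the ODDI comparison from the number of infants actually randomised with T5 ODDI above 106%, and state the sidedness and any baseline correlation relied on.
2. Define the continuous analyses by deformity at T5: ODDI change in plagiocephaly or mixed forms, and CPI change in brachycephaly or mixed forms. T5 measurements precede randomisation, so the comparison within each set remains randomised.
3. Keep full recovery, already planned, as the outcome that covers every infant.
4. Report the all-infant ODDI and CPI change analyses alongside.

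The change is to wording and reporting; no further data are needed. Its cost is fewer infants in each continuous analysis, with power that may be higher or lower than in the all-infant analysis, depending on the variance and effect in brachycephaly-only infants. The gain is an effect that can be read on the index that measures the deformity, and a correct power figure.

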### Statistical analyses

Data analyses will be performed using SPSS 18.0. A statistical significance level of 0.05 will be used and missing values will be imputed with multiple imputation [41].

#### *Cohort study*

Data analysis will start with descriptive statistics of baseline demographic and clinical characteristics of the total population at T0. At T5, this will be repeated for the clinical characteristics.

#### *Randomised controlled trial*

At T5, characteristics of the RCT population will be described. In a subsequent analysis, the intervention and control group will be compared with respect to prognostic factors using the independent samples *t*-test or the chi square test. The representativeness of the RCT population will be determined by comparing baseline demographic and clinical characteristics of the RCT population with those of the total eligible population at T5. Both the change score (continuous variable) and the success of recovery (dichotomous variable) will be compared between groups on an intention-to-treat basis. After analysis of covariance (ANCOVA), both multiple regression analyses (change score) and logistic regression analyses (success of recovery) will be carried out with predictor variables to control for confounders. Finally, a per-protocol analysis will be performed.

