Since the condition of interest changes over time and the decision-making is time-dependent, the RCT needs to be nested in a cohort study [30-32]. The decision to start helmet therapy is usually taken at 5 to 6 months of age. Recruitment at that stage is complicated as the children tend to be scattered among various institutes if their parents prefer helmet therapy or are outside the health care system if their parents choose not to start helmet therapy. As the cohort study recruits children at risk of disease progression before helmet therapy can be prescribed, we tackle this problem and we are also able to predict the number of children that ultimately will be eligible for helmet therapy and identify prognostic factors.

Additionally, nesting the RCT in a prospective cohort study makes it possible to present information on the representativeness of the RCT population, by comparing this population with non-participants [33,34]. Furthermore, outcomes of the randomised trial can be compared with the parallel non-randomised trial that employs the same types of intervention.

The main goal of the Helmet Therapy Assessment in Deformed Skulls (HEADS) study is to investigate the effects and costs of six months of helmet therapy compared to no helmet therapy in children with moderate to severe skull deformation. This article describes how this study is designed and reports the recruitment scheme so far. We provide a description of the statistical analysis plan to be used after data collection is completed and conclude with general recommendations on study design.

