### Population

Figure 1 shows that 883 infants enrolled at T0 for baseline measurement. At T5, 808 infants had a follow-up assessment; 477 did not meet the inclusion criteria for the RCT. Of these 477 infants, 26 infants had PCM outcomes above the upper thresholds of the inclusion criteria for the RCT and were eligible to participate in the nRCT. Seventy-five infants enrolled at T5 via late-enrolment, of whom 5 infants had PCM outcomes above the upper thresholds of the inclusion criteria for the RCT and were eligible to participate in the nRCT. Of the eligible 401 infants, 84 (21%) were recruited for the RCT, 296 did not participate in the RCT because their parents declined to enrol them, but were recruited for the nRCT (74%) and 21 (5%) were not recruited to either of the studies. Parents signed an informed consent form before participation in the cohort study, as well as before participation in the RCT.

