Another methodological advantage of the present study design is its ability to better evaluate the representativeness of the RCT study population. Usually, RCTs have homogeneous yet very selective populations to maximize the likelihood of detecting significant differences. The cohort study of the HEADS study represents a broad population. Due to the nested study design, it is possible to determine the external validity of the RCT, by testing whether the RCT population is representative of the broad, eligible population at T5. The same can be determined for the nRCT population. Furthermore, we can study whether participants in the RCT are comparable to the nRCT participants by comparing the study outcomes and baseline characteristics in both studies.

Finally, as the decision for helmet therapy in the nRCT group was made by parents themselves, this will allow us to investigate the relationship between real-world decisions and treatment outcomes. This provides more information on the usefulness of data from non-randomised compared to randomised studies, which is relevant in comparative effectiveness research. Furthermore simultaneous analysis of data from an RCT and nRCT can strongly contribute to the generalizability of the study outcomes and the development of clinical practice guidelines as compared to single RCTs [43].

Final results of the HEADS study are expected in 2013.

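### Representativeness is judged against a total eligible population that includes the RCT infants, although the Background names non-participants as the comparator

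*Protocol article*

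**What the plan says.** In the Statistical analyses section, under Randomised controlled trial, representativeness is to be settled by "comparing baseline demographic and clinical characteristics of the RCT population with those of the total eligible population at T5". The Discussion repeats this comparator and speaks of a test: external validity is to be determined "by testing whether the RCT population is representative of the broad, eligible population at T5". The Background describes the same purpose differently, saying that representativeness will be shown "by comparing this population with non-participants".

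The Population section gives the counts: "Of the eligible 401 infants, 84 (21%) were recruited for the RCT". A further 296 infants whose parents declined the RCT "were recruited for the nRCT (74%) and 21 (5%) were not recruited to either of the studies".

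On method, the opening of Statistical analyses says only that "A statistical significance level of 0.05 will be used". The *t*-test and chi-square test are named for a different purpose, in the sentence before the one on representativeness: "the intervention and control group will be compared with respect to prognostic factors using the independent samples" *t*-test or the chi-square test. The section comparing the randomised and non-randomised trials separately plans an RCT versus nRCT comparison of baseline characteristics, and the Discussion mentions it again.

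**The concern.** A comparison of a part with the whole that contains it differs from a comparison of participants with non-participants. The article gives one in two places and the other in a third, for the same question.

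Two consequences follow. First, the overlap shrinks the visible difference by a fixed factor, whatever test is used or even if none is. A reader who takes the tabulated difference as the contrast between consenting and non-consenting families will understate it. Second, if the analyst enters the 84 and the 401 as two independent samples, the standard error is also wrong, and the test rejects too rarely.

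Both effects push towards finding no difference, that is, towards calling the RCT representative. The abstract lists representativeness among the study's methodological questions, and the Discussion presents the ability to assess it as an advantage of the nested design. Only 21% of eligible infants entered the RCT, so selective consent is a real possibility.

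**Working it through.** **Inputs.** RCT infants n = 84; eligible infants N = 401; eligible infants in the nRCT, 296; eligible infants in neither study, 21 (all from Population). Significance level 0.05 (Statistical analyses). Two-sidedness, a common SD and the normal approximation are assumptions made here.

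**Reproducing the article's counts.** 808 − 477 + 75 − 5 = 401, and 84 + 296 + 21 = 401. The RCT share is f = 84/401 = 0.209, the stated 21%. Eligible non-participants number 296 + 21 = 317.

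**Shrinkage (no test assumed).** Because the total mean is a weighted average of the two parts,

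mean(RCT) − mean(total) = (1 − f) × [mean(RCT) − mean(non-participants)],

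with 1 − f = 317/401 = 0.79. The same holds for proportions.

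**Error rate, if an independent-samples test is used.**
- Standard error that such a test assumes: √(1/84 + 1/401) = 0.120 SD.
- True standard error of the part-versus-whole difference: (317/401) × √(1/84 + 1/317) = 0.097 SD.
- Ratio: √(317/485) = 0.808.
- Real two-sided error rate: 2 × [1 − Φ(1.96/0.808)] = 1.5%.

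Simulation under no difference gave 1.46% for the *t*-test and 1.49% to 1.53% for the chi-square test. With 84 against 317 the rate was 4.98% for the *t*-test and 4.98% to 5.00% for the chi-square test.

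**Range over final counts.** The Figure 1 data are provisional. With 96 of 401 in the RCT (the recruitment target, same eligible total) the rate is 1.2%. With 84 of 432 (401 plus the 31 infants above the upper limits) it is 1.7%. With 96 of 458 (the target at the present 21% share) it is 1.5%.

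**Power, for assumed true differences between participants and non-participants.** The article gives no such difference; 0.30 and 0.35 SD are illustrative.
- Part versus whole: the test rejects when the observed difference exceeds 1.96 × 0.120 = 0.235 SD. Power is Φ[(0.79 × δ − 0.235)/0.097], which is 51% at δ = 0.30 and 67% at δ = 0.35.
- 84 versus 317: the standard error is √(1/84 + 1/317) = 0.123 SD. Power is Φ(δ/0.123 − 1.96), which is 69% and 81%.

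**Does the RCT versus nRCT comparison cover this?** It has no overlap and includes 296 of the 317 eligible non-participants (93%). However, the eligibility section also invites infants above the RCT's upper limits into the nRCT, up to 26 + 5 = 31 by the Population counts, and these are not RCT-eligible. It also leaves out the 21 eligible infants in neither study.

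**The case against.** The strongest reply is that the article never says how the comparison will be tested. The *t*-test and chi-square test belong to intervention versus control. A reader might infer that the plan fixes an invalid independent-samples test with a 1.5% error rate, but the text does not support that. A one-sample test against the total mean, taken as fixed, would run at about 2.75%, and a purely descriptive table has no error rate. A condensed article may also leave the choice of test to the full plan. This stands: the error rate and power figures are conditional. The condition is not far-fetched, since the Discussion speaks of testing and a general 0.05 level is set.

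Second, the distance between the RCT sample and its target population is a legitimate quantity. It is a known multiple of the participant versus non-participant difference, and with the correct standard error (0.097 SD) the test statistic equals that for 84 versus 317, so no power is lost. This also stands. The shrinkage alone is a matter of scale and interpretation; power is lost only through a wrong standard error.

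Third, a reader might infer that the external-validity claim rests on the overlapping comparison alone. It does not: the RCT versus nRCT baseline comparison gives selection differences another route to detection. It mitigates the problem, but for the reasons shown above it is not the same comparison.

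None of this removes the conflict over the comparator. That is stated text, not omitted detail.

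**Conclusion.** The point holds as a minor inconsistency with a foreseeable analytic consequence. What is certain from the document is that two sections name a comparator containing the RCT infants, a third names non-participants, and the overlap reduces the observed difference to 0.79 of the participant versus non-participant difference at current counts.

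Conditional on an independent-samples test at two-sided 0.05, the real error rate is about 1.5% (1.2% to 1.7% over plausible final counts). Power at the assumed 0.30 and 0.35 SD is then 51% and 67% rather than 69% and 81%. The direction favours declaring the RCT representative. The document does not establish that such a test will be run, and the effect estimates and tests of helmet therapy do not depend on this comparison.

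**What to change.** In Statistical analyses (Randomised controlled trial) and in the Discussion, name as comparator all RCT-eligible infants not in the RCT, currently 296 + 21 = 317, in line with the Background. Infants above the RCT's upper limits should not be counted in that group.

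If a contrast with the whole eligible population is still wanted, show it descriptively, or base its standard error on √(1/n − 1/N) rather than √(1/n + 1/N). Reporting the differences with 95% confidence intervals would help but is optional.

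The cost is a change of analysis wording. The article already plans to use these baseline data for all eligible infants, so no new data collection is involved.
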